## Methods

### Study Design

This study is a three-arm randomized controlled trial with an additive parallel design. Enrollment in the study is rolling and starts as early as possible in the pregnancy (by 21 weeks’ gestation). The intervention period begins at enrollment and continues to the end of pregnancy/birth (Figure 1). Data collection occurs throughout the study with surveys at baseline, the second trimester, the third trimester, and after delivery, as well as short weekly assessments. Upon enrollment in the study, participants will be randomized to one of three groups: usual WIC (arm 1; control), usual WIC + delivery of WIC-approved food (arm 2), and usual WIC + delivery of WIC-approved food plus unsweetened beverages (arm 3).

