### Dietary Intake

Dietary intake will be measured with paired assessments using the Automated Self-Administered 24-hour (ASA24) dietary recall survey [46-48]. This process has been validated by comparison to in-person 24-hour recalls and has been used by other studies of pregnant youth with low income [49,50]. At enrollment, participants will complete their first recall over the phone with the study team. A second baseline ASA24 survey will then be completed, approximately 2 to 5 days after enrollment. Participants will complete four additional ASA24 surveys using the same paired system during the intervention period. Two will be completed in the second trimester and two in the third trimester. Study team members will be available, as needed, to assist participants in completing all ASA24 surveys. Paired responses will be combined and used to calculate a Healthy Eating Index (HEI) score for each time point: baseline, second trimester, and third trimester [46,51]. The output from the ASA24 includes additional data on fruit and vegetable servings as well as other macronutrient data.

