### Data Analysis

To understand the effect of grocery delivery on pregnancy weight gain, diet quality, and health outcomes, weight will be measured weekly, dietary quality will be assessed twice per trimester, and perinatal outcomes will be assessed at the end of the pregnancy. All analyses will follow the intention-to-treat principle. Prior to analysis, assessment of missing data will be completed and appropriately imputed using multiple imputation methods [65].

Our primary outcome is appropriate weight gain in pregnancy, which is based on prepregnancy BMI and includes weekly weight gain and total weight gain recommendations. Total weight gain at birth will be categorized as above, below, or within the Institute of Medicine guidelines [5,33]. Multinomial logistic regression analysis will be used to compare the likelihood of falling above, within, or below guidelines for total weight gain in pregnancy across arms after adjusting for potential confounders such as age, race, ethnicity, socioeconomic status, and household characteristics. Confounders will be identified through significant findings in bivariate analysis comparing the three groups and by consideration of variables based on prior scientific evidence. Summary statistics of key time-dependent measures and other non–time-dependent measures will also be included as covariates. Modification of the study arm effect by key variables will be investigated through interaction terms in the regression model.

The trajectory of weight gain behavior, using each week’s categorized weight gain (within guidelines vs not), will additionally be assessed as the outcome in a clustered logistic regression model fit using a generalized linear mixed model framework. The study arm is the primary between-participant factor, while time (week) is the main within-participant covariate. The interaction term between time and arm is also a factor of interest, as it will allow us to assess changes in weight gain behaviors over time between study arms. A random participant-level intercept will account for within-participant clustering, and a random slope for time will be investigated to account for additional between-participant variability. Additional covariates and effect modifiers included in these regression models will be chosen using the same methods as before.

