Our secondary outcome is diet quality as measured by the HEI score based on two ASA24 measurements at baseline and in the second and third trimesters [51,66]. A comparison of overall HEI scores between study arms will be carried out using separate linear mixed models with calculated HEI scores from each trimester as the outcome. As before, the study arm will be the primary between-participant factor; time, as measured by trimester, the within-participant covariate; and the interaction between arm and time will be assessed to measure the difference in trimester effect between the arms. Random participant-level intercepts and slopes for time will assess the deviation from the overall average and account for any within-participant clustering. Models will be adjusted for additional confounders and covariates, determined as in prior models. Fruit and vegetable intake, as well as other macronutrient details, will also be evaluated.

Prenatal complications, delivery complications, and birth weight (small/large for gestational age) are also secondary outcomes that will be assessed. Comparison of the proportion of participants with complications between study arms will be analyzed using a logistic regression model in a manner analogous to the primary outcome of appropriate weight gain in pregnancy.

The end-of-study interview transcripts will be analyzed using standard qualitative techniques [67-69]. Two investigators will review all transcripts, create memos of major concepts present, and iteratively develop a codebook. Transcripts will be coded and major themes and conclusions determined by consensus. Themes identified from these transcripts will describe participants’ satisfaction or dissatisfaction with delivery, perceived impact of food delivery on their health and diet, and other challenges/barriers to healthy behaviors during pregnancy. The interviews will be used to provide context and narrative to inform findings from quantitative outcome data, and will be used in dissemination to tell the participants’ perspective regarding the impact of grocery delivery.

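### The HEI analysis is specified both as separate models per trimester and as one longitudinal model; the joint reading leaves baseline as a free outcome and gives away precision

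*Protocol article*

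**What the plan says.** The Data Analysis section of the protocol article describes the diet-quality analysis in consecutive sentences. HEI scores are to be compared between arms "using separate linear mixed models with calculated HEI scores from each trimester as the outcome". Study arm is then the between-participant factor, with "time, as measured by trimester, the within-participant covariate". An arm-by-time term is specified in the same sentence: "the interaction between arm and time will be assessed to measure the difference in trimester effect between the arms". The random part follows: "Random participant-level intercepts and slopes for time will assess the deviation from the overall average".

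The Dietary Intake section says how many scores there are. Paired recalls are combined into one HEI "score for each time point: baseline, second trimester, and third trimester". Of the four recalls after baseline, "Two will be completed in the second trimester and two in the third trimester".

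On timing, the eligibility list in Participants allows gestational age up to 20 weeks, and Study Design says enrolment starts "as early as possible in the pregnancy (by 21 weeks" of gestation). The opening of Data Analysis summarises the schedule as "dietary quality will be assessed twice per trimester".

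**The concern.** The two descriptions of the model exclude each other, and the choice between them changes what is estimated. Separate models give an arm difference within each trimester, with baseline analysed as an outcome in its own right. The joint model gives a difference between arms in change over time. An analyst following the text must decide which was meant, and that should be settled before outcome data are seen.

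Once the joint reading is taken, two further points arise. First, the pre-randomisation HEI score enters as one of the repeated outcomes, and its arm means are left free. The design already guarantees equal expected baseline means, and this model does not use that. The cost is precision on the diet comparison, which is part of both stated hypotheses. Second, trimester does not uniquely label the three assessments when a woman may enrol in her second trimester.

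**Working it through.** The article gives no sample size or power figure for HEI, so there is no stated number to reproduce. The check is whether each model can be fitted, then what the fitted contrast costs.

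**1. Can each reading be fitted?**

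Inputs: 3 arms (Study Design); 3 time points with one HEI score each (Dietary Intake); fixed effects for arm, time and arm-by-time, plus a random intercept and slope (Data Analysis).

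Fixed-effect parameters:
- Time categorical: 1 intercept + 2 arm + 2 time + 4 interaction = 9.
- Time linear: 1 intercept + 2 arm + 1 time + 2 interaction = 6.

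Covariance parameters: intercept variance, slope variance, their covariance and residual variance = 4.

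| Model | Fixed-effects rank, time categorical | Fixed-effects rank, time linear | Variances and covariances available |
|---|---|---|---|
| Separate, one trimester | 3 of 9 | 3 of 6 | 1, for 4 parameters |
| Joint, three time points | 9 of 9 | 6 of 6 | 3 variances + 3 covariances = 6, for 4 parameters |

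In a separate model only the three arm means are estimable. The time effect, the interaction and the random slope are not, and the random intercept cannot be told apart from the residual. The joint model is identified in full.

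**2. What does the joint contrast cost?**

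Assume complete data, equal variance σ² at baseline and follow-up, and within-person correlation ρ (after any other covariates). For one follow-up occasion, the variance per participant is:
- difference in change: σ² + σ² − 2ρσ² = 2σ²(1−ρ);
- baseline-adjusted: σ²(1−ρ²).

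The ratio is 2(1−ρ)/(1−ρ²) = 2/(1+ρ). The share of information lost is 1 − (1+ρ)/2 = (1−ρ)/2.

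| ρ (assumed) | Variance ratio | Information lost |
|---|---|---|
| 0.3 | 2/1.3 = 1.54 | 35% |
| 0.4 | 2/1.4 = 1.43 | 30% |
| 0.5 | 2/1.5 = 1.33 | 25% |
| 0.6 | 2/1.6 = 1.25 | 20% |

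The article gives no value of ρ.

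**3. Does trimester identify the assessment?**

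The article does not define the start of the second trimester. If it is taken as week 13 or 14, enrolment through week 20 leaves a window of 8 weeks (13 to 20) or 7 weeks (14 to 20) in which the baseline recalls are themselves second-trimester recalls. Such a woman has a baseline pair and a follow-up pair in the same trimester and none in the first, so the summary of two recalls per trimester is not true of her. The share of women affected depends on the enrolment distribution, which the article does not give.

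**The case against.** The strongest reply is that one loose word carries the contradiction. Everything after it describes a longitudinal model in the style of the weekly weight model just before it, and *separate* may mean separate from the weight models. That is the likely intention, and it means that the plan as a whole is not unfittable. But the sentence ties the separate models to the scores of each trimester, so it still has to be corrected.

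On the time label, Table 1, Dietary Intake and the first sentence on HEI in Data Analysis all list baseline as its own time point. Trimester is therefore probably shorthand for the three assessments. A reader might infer that baseline and on-treatment scores will be pooled under one second-trimester code. No sentence says so; this is a risk of the wording, not a stated rule.

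A reader might also infer that the arm effect is diluted because it is averaged over a baseline at which no effect is possible. That does not follow. The stated contrast is the arm-by-time interaction, and with baseline as its own level that contrast is not diluted.

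Nor do the documents support a concern that baseline recalls are taken after assignment: the Randomization section places assignment after the baseline diet recalls.

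Finally, it can be said that difference in change is a valid estimand and that baseline handling is detail for the full protocol or SAP. The validity stands. But the article does more than stay silent: it fixes an interaction contrast with baseline among the outcomes, and the more precise alternative uses data already being collected.

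**Conclusion.** The point holds as an inconsistency in the stated HEI model, with a moderate precision cost under the reading that can be fitted. Separate per-trimester models cannot contain the time, interaction and random-slope terms listed; one joint model can. In the joint model the arm-by-time contrast is unbiased, but for assumed ρ of 0.3 to 0.6 its variance at each follow-up is 1.54 to 1.25 times that of a baseline-adjusted contrast. Those figures rest on equal variances, complete data and a correlation that the article does not state. The ambiguity of trimester as the time variable is real, but its extent cannot be quantified from the article.

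The scope is one secondary outcome. The primary weight-gain analysis and the sample size are unaffected.

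**What to change.** Amend the HEI paragraph in Data Analysis as follows:

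- Delete *separate* and state that one linear mixed model is fitted to the HEI scores.
- Code time as assessment occasion (baseline, second-trimester assessment, third-trimester assessment), not as trimester of pregnancy. Reword the summary of two recalls per trimester to match.
- Either keep baseline among the outcomes with its mean constrained equal across arms, or use baseline HEI as a covariate and model the two follow-up scores.
- Report arm differences at the second- and third-trimester assessments.

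If the covariate option is chosen, the random part must change too. Two follow-up scores supply 2 variances + 1 covariance = 3 quantities, too few for the 4 parameters of a random intercept, random slope and residual. An unstructured within-person covariance would serve.

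The cost is a wording change made before analysis. It needs no new data or visits and no change in sample size.

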## Results

This study was funded in April 2021, data collection started in December 2021, and data collection is expected to be concluded in 2026. No results are available as of manuscript preparation.

## Discussion

This protocol describes a randomized controlled trial to evaluate whether grocery delivery of healthy WIC-approved foods supports healthy pregnancy weight gain for young pregnant women with low income. We will additionally evaluate if the grocery delivery impacts diet quality, pregnancy complications, and delivery outcomes. We anticipate that the young pregnant women in the two intervention groups will have better rates of appropriate pregnancy weight gain, improved diet quality, and lower rates of pregnancy and delivery complications.

Results from this study can be used to inform United States Department of Agriculture policies on online use of WIC benefits as well as to provide evidence about the cost-effectiveness of national implementation of grocery delivery for WIC beneficiaries [32]. These outcomes may additionally provide evidence to clinical practices or health systems on opportunities for the use of food delivery programs within their patient populations to address social determinants of health.

There are several key strengths to this protocol. This work uses a low-cost well-established service to enhance an existing government program which enables the results to inform policies to improve the implementation of WIC services and other programs for vulnerable populations. COVID-19 has also led to a surge in online grocery ordering, which enhances the generalizability of this study [31]. Additionally, this study uses low-burden communication and data collection methods to allow for high levels of participant retention.

Limitations of this study are that it does not perfectly emulate the real-life application of integrating grocery delivery into WIC services, as study personnel are ordering and managing the delivery process, which reduces the generalizability of the results to program-based implementation. Specifically, participants request the groceries from the study team who then place the orders and manage the deliveries. Additionally, participants are able to access and use their WIC food benefits in addition to groceries provided, and it does not directly replace this benefit.

Ultimately, this study will provide rigorous evidence regarding the impact of grocery delivery of healthy foods and unsweetened beverages among pregnant young women with low income and their infants. The findings from this study will provide invaluable information about the potential benefits of incorporating grocery delivery in WIC and about the costs to implement, sustain, and expand such a program.

## Appendix

Multimedia Appendix 1 Peer Review Report from the Community-Level Health Promotion (CLHP) Study Section - Healthcare Delivery and Methodologies Integrated Review Group - Center For Scientific Review (National Institutes of Health, USA).

## Abbreviations

ASA24: Automated Self-Administered 24-hour
HEI: Healthy Eating Index
SSB: sugar-sweetened beverage
WIC: Special Supplemental Nutrition Program for Women, Infants, and Children
